### Group 2 (wait-list)

The clinician baseline assessment for Group 2 is identical to that for Group 1. The Group 2 assessment occurs at 0–3 months (concomitant with the Group 1 clinician baseline) and again at 9–12 months (concomitant with the Group 1 post-intervention assessment.)

Group 2’s clinician training intervention occurs in the same manner as described in the section, Description of Intervention (section 2.11) for Group 1. Standardization of both Group 1 and Group 2’s training intervention sessions is assessed by audio-recording all sessions and ensuring that the key objectives of each session are met using a pre-developed checklist and via rating by a trained research staff member not involved in delivering the intervention.

Group 2’s Post-Intervention Assessment occurs immediately post-intervention and at six months post-intervention in the same manner as described previously for Group 1 (section Post-Intervention Clinician Assessment). As with Group 1, Group 2 clinicians also complete a survey asking about the feasibility of the intervention and individual exit interviews.

### Evaluation and measures

#### Primary outcome measure: 5As score

The primary outcome measure is the 5As score, a score of the frequency and quality of 5As discussions about physical activity. Based on our previous pilot study and others’ published work [11,15,53,54] we developed a coding form to capture the 5As from audio-recorded office visit discussions. The 5As score has two components: 1) the sum of each A of the 5As occurring in each office visit when the topic of physical activity is raised (range 0/no As used to 5/all As used) and 2) a rating of the quality of each A when it occurs (ranging from 1–3 based level of detail from minimal to intensive). The 5As score is measured at baseline, immediately post-intervention, and at six months follow-up for Groups 1 and 2. The 5As score is assessed by trained research staff blinded to clinician and time point.

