The second component in the conceptual framework is patient-centered communication (PCC) [36,37]. Patient-centered communication directly addresses barriers in counseling for underserved populations that may not be adequately captured in the 5As alone. Understanding patients’ social context might help narrow the gap in the social distance between patient and physician. For example, miscommunication can occur if clinicians give advice without understanding the patient’s life situation, without encouraging the patient to ask questions and take an active role, and without reinforcing the patient’s learning during the office visit by summarizing, checking, and verifying mutual understanding [38]. PCC improves trust, [16] motivation, adherence and control of some chronic illness [17,18] however its application to physical activity counseling is less well understood. PCC consists of several constructs; [39-44] for this project, we focus on the constructs overlapping with SDT of (1) autonomy support, defined as activating and involving patients in choices about their care [45] such that they feel supported and empowered, [46] and (2) understanding patients’ social context.

Table 1 summarizes how self-determination theory, the 5As, and patient-centered communication inter-relate in the project. In the intervention’s design, interactive group and peer discussions are incorporated into the training techniques to increase both clinician and patient motivation for physical activity discussion. This training technique relates to the 5As and PCC by increasing clinician motivation to ASK, ADVISE, and ASSESS their patient’s physical activity via the use of patient-centered communication skills of supportive listening and open-ended questions. The intervention is designed to provide a choice of options and community resources for clinician to ASSIST and ARRANGE referral for physical activity, thus aiming to increase clinician autonomy supportiveness and competence to counsel. In the assessment and measurement, SDT, the 5As and PCC inter-relate in the analysis of the discussions via ratings of the content of the physical activity discussions (using the 5As), and the quality of the physical activity discussions (whether they were autonomy supportive-SDT, and whether they explored the clinician made supportive statements, and verified understanding and agreement-PCC).

**Table 1 T1:** Summary of intervention components and corresponding conceptual framework

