	**Self-determination theory**	**5As**	**Patient-centered communication (PCC)**
Design of intervention (key concepts)	· Promoting autonomy supportive skills for clinicians when counseling patients about physical activity	· Use of 5As for physical activity counseling	· Understanding patients’ social context
			· Offering support
			· Encouraging patient participation
	· Increasing clinician perceived competence to counsel		
Intervention training (curriculum components)	· Interactive discussion on strategies to increase both patient motivation for physical activity and clinician motivation to raise the topic	· Introduction, repetition, and reinforcement of each of the 5As via didactic presentation, role play, and standardized patient feedback	· Role play and group discussion to develop and reinforce supportive listening and open-ended questions about physical activity
	· Offering a choice of community resources for referral		
	· Offering a choice of optional electronic health records tools and eliciting ongoing feedback		
			· Use of standardized patients to give feedback to clinicians on PCC skills
Assessment/measurement (clinician perspective)	Clinician surveys and interviews	Clinician interviews asking about recall of 5As	Clinician surveys and interviews
Assessment/measurement (patient perspective)	Patient ratings of autonomy support of clinicians, perceived competence for physical activity	Patient report of 5As discussions of physical activity	Patient ratings of trust and satisfaction with their relationship with their clinician; patient interviews on communication skills of their clinicians
Assessment/measurement (blinded coder)	Coding of autonomy supportiveness (global rating and for each A)	Coding of content and quality ratings for the 5As	Coding of supportive statements, exploration of patient’s social context related to physical activity, encouraging questions, verifying understanding and agreement

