The purpose of this paper is to describe a study protocol of a clinician training intervention to improve physical activity counseling in underserved primary care settings using the 5As. Aim 1 of the project assesses whether a 5As physical activity communication training intervention increases communication skills during visits underserved patients in the post-intervention period (immediately post and at one year compared to baseline). Aim 2 assesses whether the 5As communication training intervention improves patients’ perceived competence for physical activity. Aim 3 assesses whether the 5As communication training intervention improves clinicians’ autonomy support for physical activity with their patients. Aim 4 assesses whether clinicians and patients perceive the 5As counseling to be feasible and sustainable and whether the communication training addresses pertinent barriers to promoting physical activity.

The hypotheses are as follows:

H1: Clinicians who complete the communication intervention will increase their use of all 5As for visits in which the topic of physical activity is raised as judged by comparing the audio-recordings of office visits in the post-intervention period (immediately post and at one year) compared to baseline.

H2: The intervention will increase clinician autonomy supportiveness when counseling about physical activity.

H3: The intervention will increase patient perceived competence for adopting physical activity.

H4: Specific patient recall of the Assist and Arrange will be associated with the greatest patient perceived competence to adopt physical activity compared to recall of Ask, Advise, or Assess.

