### Statistical analyses

The primary outcome measure will be the 5A score as described in (section Primary outcome measure: 5As score). The primary analysis will use a mixed effect model to compare mean 5As scores between and within each group for each of the three time points: baseline, immediately post-intervention, and follow-up. The primary hypothesis (H1) is: Clinicians who complete the communication intervention will increase their use of all 5As for all visits in which the topic of physical activity is raised as judged by audio-recordings of office visits in the post-intervention period (immediately post and at one year) compared to baseline. Figure 2 shows the analysis plan for hypothesis testing and exploratory outcomes.

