### Sample size and power

The primary goal of this study is to evaluate the influence of a clinician communication intervention on use of the 5As in communication about physical activity in the post-intervention period (immediately post and at one year) compared to baseline as assessed by audio-recorded data. The sample includes a planned maximum of 15 clinicians (eight in Group 1 and seven in Group 2) measured at three (Group 1) or four (Group 2) time points. The measurements consist of a total of 25 audio-recorded patient visits from each clinician distributed across each of the evaluation points: approximately 10 recordings at baseline and seven or eight each at post- and follow-up points. Of the planned 375 recorded visits, we estimate up to 20% may be excluded from the analysis due to the patient or clinician shutting off the recorder, or equipment malfunction, thus leaving approximately 300 recorded visits (about seven per clinician per time point, or 20 total per clinician) for analysis. Pilot data with 46 recorded visits from eleven physicians showed that the average 5A score was 0.74, with a standard deviation of 1.06. Thus, with 15 clinicians and 20 patients per clinician, we will have 80% power to detect a difference of 0.54 between Groups 1 and 2, using a two-sided t-test at 0.05 significance level.

The final analyses will use a mixed effects model to incorporate correlations between the observations made by the same physician. The variance in 5A scores taken from patients within a single physician's patient panel will likely be smaller than the variance of scores taken from patients between different physicians, i.e. the intraclass correlation coefficient (the ratio of between-physician variance to the sum of between- and within-physician variances) will be larger than zero. We have conducted a series of power analyses taking this clustering into effect using a Mann–Whitney two-sample t-test of means.

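### The primary 5As score is defined over visits in which physical activity is raised, which the training aims to increase, and this conflicts with the all-recordings basis of the power calculation

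*Protocol article*

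**What the plan says.** Primary outcome measure: 5As score gives the outcome two components. The first is "the sum of each A of the 5As occurring in each office visit when the topic of physical activity is raised", running from 0 to 5. The second is "a rating of the quality of each A when it occurs", on a scale of 1 to 3.

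H1 carries the same condition twice. The hypotheses listed before the Methods refer to "use of all 5As for visits in which the topic of physical activity is raised", and Statistical analyses refers to "use of all 5As for all visits in which the topic of physical activity is raised".

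Raising the topic is a stated target of the training. Table 1 lists as a curriculum component "Interactive discussion on strategies to increase both patient motivation for physical activity and clinician motivation to raise the topic", and the text on Table 1 describes "increasing clinician motivation to ASK, ADVISE, and ASSESS".

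Sample size and power plans 375 recordings and removes up to 20% for recorder shut-off or equipment failure only. It carries about 300 visits (20 per clinician) into the analysis. Its variance input is introduced with "Pilot data with 46 recorded visits from eleven physicians showed that the average 5A score was 0.74", with an SD of 1.06. The Abstract likewise says the outcome is judged by evaluating 375 recorded visits.

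**The concern.** If only visits with a discussion are scored, whether a visit enters the primary analysis depends partly on what training does. Randomising clinicians does not make the selected visits comparable between groups, and the visits selected before and after training differ in kind. The mixed model (group, time, baseline score, random clinician effect) does not address this.

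Two things are at stake. First, a clinician who moves from not mentioning activity to mentioning it briefly has changed in the intended direction. The restricted score omits the earlier silent visits and averages in the new brief ones. Second, the visits used for power are not the visits named in H1.

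**Working it through.** **1. The plan's own power figure.** Inputs from Sample size and power: 8 and 7 clinicians, 20 visits each, SD 1.06, difference 0.54, two-sided 0.05, 80% power. The detectable difference is (1.960 + 0.842) × SD × √(1/n1 + 1/n2).

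- 160 v 140 visits: 2.802 × 1.06 × 0.1157 = 0.344, and power for 0.54 is 99.3%.
- 56 v 49 (seven per clinician at one time point): 0.581, power 74.0%.
- 64 v 56 (eight per clinician at one time point): 2.802 × 1.06 × 0.1830 = 0.543, power 79.5%.

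The stated 80% does not follow from the literal inputs. It appears with eight visits per clinician at one time point, or at 20 per clinician with an unstated ICC of about 0.077. That is a separate matter. What counts here is that every layout uses all usable recordings.

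**2. What the pilot figures imply.** Take the pilot score as an integer count from 0 to 5 with mean 0.74 and mean square 1.06² + 0.74² = 1.6712. The share scoring at least 1 is then bounded:

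- lowest with values 0, 2, 3: 0.2744 + 0.0637 = 0.338
- highest with values 0, 1, 5: 0.5072 + 0.0466 = 0.554

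So about 45% to 66% of the averaged visits scored 0. This suggests that visits without discussion were included, but does not prove it.

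**3. Sample if only raised visits count.** Assume the raised share equals that range. Then 300 × 0.338 = 101 and 300 × 0.554 = 166 visits remain. At seven recordings per clinician per time point, 2.4 to 3.9 are usable.

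**4. Power under that assumption.** In the 64 v 56 layout with SD held at 1.06, the sample becomes 21.6 v 18.9 up to 35.4 v 31.0. Power for 0.54 is about 37% to 54%, and the detectable difference is 0.93 to 0.73.

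The SD among raised visits need not be 1.06. If every pilot zero was a visit without discussion, the moments give:

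| Share raised | Mean among raised | SD among raised | Detectable difference |
|---|---|---|---|
| 0.338 | 2.19 | 0.39 | 0.34 |
| 0.40 | 1.85 | 0.87 | 0.70 |
| 0.50 | 1.48 | 1.07 | 0.78 |
| 0.554 | 1.34 | 1.11 | 0.76 |

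The sample falls in every row. Precision usually worsens, but not at the lower extreme. A difference of 0.54 among raised visits is also not the same quantity as 0.54 over all visits.

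**5. Direction of the selection effect.** Assumed rates: topic raised in 40% of visits before training with a mean of 1.85 As (0.40 × 1.85 = 0.74), and in 70% after.

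| Existing conversations after training | Added conversations | All-visit mean (change) | Raised-visit mean (change) |
|---|---|---|---|
| 1.85 | 1.0 | 0.74 + 0.30 = 1.04 (+0.30) | 1.04 / 0.70 = 1.49 (−0.36) |
| 1.85 | 1.85 | 1.295 (+0.555) | 1.85 (0) |
| 1.85 | 2.5 | 1.49 (+0.75) | 2.13 (+0.28) |
| 2.49 | 1.0 | 0.996 + 0.30 = 1.30 (+0.56) | 1.85 (0) |

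In the first three rows the conversations that would have happened anyway do not change, yet the restricted score falls, stays put or rises according to the added ones alone. In the fourth row those conversations improve and more take place, and the restricted score shows nothing.

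**The case against.** The strongest reply is that nowhere does the article say that visits without discussion are dropped. The only exclusions listed are recording failures, about 300 visits go forward for analysis, and the score range begins at 0 for no As used. On that reading a silent visit scores 0, and both the selection effect and the power mismatch vanish. The coding form is not shown and may settle the matter. This reply has force, but it contradicts both statements of H1, so the text needs correcting on either reading.

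Several stronger inferences are tempting and are not supported:

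- A reader might infer that training will look harmful. The negative row above assumes brief added conversations and no gain in existing ones, although the sessions rehearse every A. Other inputs give zero or positive changes.
- A reader might take the 0.74 as averaged over all 46 pilot visits. The sentence does not say so.
- A reader might equate raising the topic with the Ask step. A patient can raise it, so a raised visit may score 0. If 0.74 is an all-visit mean, the raised share could then exceed 0.55.
- A reader might call the quality rating defective. Rating detail only when an act occurs is a natural definition, but the result is conditional and should be labelled so.

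**Conclusion.** The concern holds in this form: the outcome definition and H1 restrict the primary score to visits in which activity is raised, the training targets that event, and the power section counts all usable recordings. Applying H1 as written conditions the comparison on a post-randomisation effect of training and cannot capture how often the topic is discussed. The direction and size of any distortion cannot be determined from the document.

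The drop from about 300 to 101–166 visits rests on treating the pilot score as a simple count averaged over all pilot visits, with zeros meaning no discussion. The 37% to 54% power range also requires the SD to stay at 1.06, so it is an illustration and not an estimate. Neither figure is needed for the main conclusion, which rests on the wording and the stated aim of the training.

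**What to change.** - Define the primary count component as the number of As (0 to 5) in every usable recorded visit, scoring 0 when physical activity is not raised.
- Reword H1 in both places to refer to all usable recorded visits, in line with Sample size and power.
- Report as supportive descriptive results the proportion of visits with the topic raised, the score among those visits, and the quality rating given when an A occurs. State that the last two are conditional on discussion.
- State whether the pilot mean and SD were taken over all 46 visits, so that the variance input matches the revised outcome.

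The cost is small: a change of wording and a zero-scoring rule applied to recordings that are to be evaluated anyway. The outcome will contain more zeros, which the model check must allow for. Inference would rest on the count, with quality as support, so the description of the primary outcome as frequency and quality needs a matching edit. Recruitment of clinician participants allows baseline recording to run beyond 10 visits when no discussion is captured. Those extra recordings must be kept and scored, zeros included.

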#### Secondary outcome measures

The Perceived Competence Scale (PCS) measures the self-determination construct of patient perceived competence in their ability to increase their level of physical activity [17]. The PCS is a four item (Alpha reliability = 0.90) validated psychometric instrument to measure a person’s feelings of competence at carrying out a physical activity [55,56]. The PCS is administered to patients at baseline, post-intervention and follow-up as part of the post-visit survey’.

The Modified Health Care Climate Questionnaire (mHCCQ) [17] is a patient reported measure of the degree to which the clinician provides autonomy support, a construct derived from self-determination theory shown to be modifiable in health behavior interventions. The mHCCQ is a six item validated psychometric instrument that has been shown to be associated with behavior change for smoking cessation, weight loss and maintenance, and exercise. The mHCCQ measures patient perceptions of providers as autonomy supportive versus controlling and has been validated for use in primary-care offices (Alpha reliability is 0.92) [57]. The mHCCQ is administered at baseline, post-intervention and follow-up.

Clinicians’ perspectives on the intervention’s feasibility, sustainability, and learning objectives acquired, is assessed three ways: (1) via a survey administered at baseline and post-intervention, (2) via a process evaluation throughout the training period, and (3) via individual clinician post-intervention interviews. For the survey, we use a previously published survey from the Physical Activity for Life (PAL) study, which is a 20 item face-valid questionnaire to explore clinician impressions of the effectiveness of the intervention [13]. The survey contains items asking about clinician perspectives on feasibility, knowledge, and skills gained from the intervention. Ongoing process evaluation data are collected throughout the intervention’s training sessions in the form of field notes and audiorecorded feedback from clinicians during the training sessions. At the conclusion of the study, the principal investigator and research assistant conduct individual interviews to elicit clinician perspectives on feasibility of the intervention, relevance of training objectives, and suggestions for improvement.

#### Exploratory outcome measures

Moderation variables consist of patient factors and visit factors. Patient factors are socio-demographic variables, body mass index, baseline health, [58,59] health literacy[60], co-morbidities, and length of relationship with their clinician. Visit factors consist of type of visit, measured categorically using the clinic schedules (e.g. routine follow-up, health care maintenance) and competing demands measured by the 1) number of topics discussed and 1) number of health behaviors discussed.

Mediation variables consist of patient perceived competence for physical activity (using the PCS), clinician autonomy support (using the mHCCQ) for physical activity, and patient recall of 5A using the Physical Activity Exit Interview (PAEI) [47]. The PAEI is a 12-item survey administered to patients after their visit asking them to recall specific content (Yes/No) to questions corresponding to each A for physical activity, such as “Did your doctor advise you to become more physically active?”, “Did your doctor discuss difficult situations you might encounter or problems you might have in trying to become more physically active?”, and “Did your doctor state that he/she is planning to discuss your physical activity on a future visit?”

### Data management

All questionnaires and measurements will be collected and entered into a secure protected database by the Research Assistants. Data will be entered on scannable forms and electronically sent to an Access database. After scanning, data will be audited visually for errors. SAS statistical packages are used for the analyses. Unless otherwise stated, all statistical tests will be performed at the two-tailed 5% level of significance. Likewise, 95% confidence intervals will be constructed for estimation of effects (e.g., difference in mean 5A scores across time points).

#### Assumptions

The assumptions underlying all statistical analyses will be thoroughly checked using appropriate graphical and numerical methods [61,62]. If outliers or influential data are detected, the accuracy of the data will be investigated. If no errors are found, analyses may be repeated after removing these cases to evaluate their impact on the results. However, the final analyses will include these data points.

